### Data analysis

The primary and secondary outcome measures will be assessed for immediate and long-term effects using two-factor multivariate analysis of variance (MANOVA), with repeated measures for time. For all multivariate ANOVA tests described, significant main effects will be reported if there are no significant interactions. If significant interactions are found, then one-way ANOVAs will be performed for each main effect. Post-hoc testing will be performed (as necessary) to determine statistically significant pairwise comparisons. Statistical analysis of the results will be performed using the SAS system, version 8.2 (SAS Institute Inc., Cary, NC, USA). All significance levels will be set at p < 0.05.

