### Outcome measures

We have used the International Classification of Functioning (ICF) conceptual framework [31,32] to classify the study's outcome measures (Figure 6). The ICF framework categories (body functions and structures, activity, participation) correspond, respectively, to Nagi's disablement model [32,33] categories (impairments, functional limitation, disability). We divided the outcome measures into primary and secondary variables. The primary outcome measures will provide an assessment of the intervention and the secondary outcome measures are descriptive, informing, and hypothesis-building. Testing of all outcome measures will be administered at the post-surgical/pre-intervention assessment, post-intervention assessment, and 1-year post-surgical assessment. In addition, completion of questionnaires and pain visual analog scales (VASs) will occur every six months after the 1-year post-surgical assessment, for the remaining four years of the study.

The subject must complete all sections of each questionnaire for the questionnaire to be considered valid. Research personnel will ensure that all sections are completed during each assessment. Incomplete questionnaires will not be accepted for data entry.

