The Passive Straight Leg Raise Test (PSLR) will be used to assess the mechanical movement of the nerves in the lower extremity and to assess symptoms [52,53]. The PSLR will be quantified using a goniometer to measure hip flexion ROM, and a pain VAS to quantify pain complaint. In addition, a crossed straight leg raise (CSLR) sign, in which elevation of the leg produces symptoms on the contralateral spine and/or leg [54], will also be noted. The PSLR test has been shown to have high sensitivity (i.e., a negative PSLR is highly indicative of no presence of a herniated lumbar disc) and low specificity (i.e., a positive test is not highly indicative of the presence of a herniated disc). On the other hand the CSLR sign has been show to have a low sensitivity (0.29) and high specificity (0.88) [54]. A positive PSLR will be considered one in which a patient's symptoms are reproduced by ankle dorsiflexion.

Lower quarter flexibility/muscle length measurements will be assessed to determine the effect of the intervention on muscle flexibility, and will be derived from the amount of movement attained at the relevant joint for each muscle group. Lumbar spine range of motion (ROM) will be used to quantify lumbar spine mobility during forward flexion, extension, and right and left lateral flexion for each subject. Due to post-surgical restrictions, lumbar ROM will only be measured immediately following the intervention and one year after surgery. Post-surgical restrictions are in place to prevent the patient's mobility from compromising the surgery. Lumbar spine ROM in the sagittal plane will be assessed using a double inclinometer method, which has been proven to be a highly reliable and valid measurement technique [55]. Lumbar spine ROM in the frontal plane will be assessed using a tape measure.

Lumbar spine instability will be tested to gain information on the nature of the subject's symptoms. With the subject's torso prone on a treatment table and both lower extremities on the floor, the examiner will apply posterior-to-anterior (P-A) pressure at each lumbar spinous process to the end of the perceived range of motion. Reproduction of pain, and the involved segment, will be noted. If the subject reports a full reduction of symptoms at the painful segment when lifting the LEs, it will be considered a positive test for instability of that segment. The prone instability test has been shown to be more reliable than the segmental instability test [56].

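### The Data analysis section applies one repeated-measures MANOVA at p < 0.05 to all outcomes, which blurs the descriptive role given to the secondary measures and does not suit several of them

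*Protocol article*

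**What the plan says.** **Roles (Outcome measures).** The article divides its outcomes into two tiers. Of the first it says "The primary outcome measures will provide an assessment of the intervention"; of the second, "the secondary outcome measures are descriptive, informing, and hypothesis-building".

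**Analysis (Data analysis).** Both tiers get one rule: "The primary and secondary outcome measures will be assessed for immediate and long-term effects using two-factor multivariate analysis of variance (MANOVA", time being the repeated factor. Then: "For all multivariate ANOVA tests described, significant main effects will be reported if there are no significant interactions". A significant interaction leads to one-way ANOVAs, and "Post-hoc testing will be performed (as necessary) to determine statistically significant pairwise comparisons". The section closes with "All significance levels will be set at p < 0.05". No sentence treats the secondary tier differently.

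**The secondary measures (Secondary outcome measures).** Eight are named: fear-avoidance questionnaire, 24-hour activity scale, 5-minute walk, lower-quarter neurological screen, straight-leg raise, flexibility, lumbar range of motion and lumbar instability. Of the instability test, the article says that if symptoms fully resolve on lifting the legs "it will be considered a positive test for instability of that segment". Lumbar range of motion is taken only after the intervention and at one year, because of post-surgical restrictions. Flexibility "will be assessed to determine the effect of the intervention on muscle flexibility".

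**The concern.** A tier described as descriptive and hypothesis-building is given the same inferential treatment as the tier that is to assess the intervention: same model, same level, same follow-on tests, no exploratory label. A significant secondary result could then be presented as an intervention effect with the Data analysis section as its authority.

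Separately, the rule covers every secondary measure, and for some it cannot be sensibly applied. MANOVA assumes roughly continuous, multivariate normal responses, and a repeated-measures version needs the response at each modelled visit. Yes/no signs and ordered grades fail the first condition. Lumbar range of motion fails the second for any model that starts before the intervention.

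**Working it through.** The core of this point is a comparison of sections, not arithmetic.

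**Step 1. Does the stated method suit each secondary measure?**

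| Measure | Form given in the article | Suits a pre/post repeated-measures MANOVA? |
|---|---|---|
| Fear-avoidance questionnaire | questionnaire, taken here as a numeric score | yes, in form |
| 24-hour activity scale | time spent by activity type | yes, in form |
| 5-minute walk | distance | yes, in form |
| Flexibility | amount of joint movement | yes, in form |
| Straight-leg raise | angle and pain VAS; also a positive test and a crossed sign | angle and VAS yes; the two signs no |
| Neurological screen | sensation, manual muscle tests, reflexes | no |
| Lumbar instability | positive or negative | no |
| Lumbar range of motion | numeric, but only post-intervention and one year | no |

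So 4 of 8 measures do not fit, in whole or in part. That reflexes and muscle tests are ordered grades is the usual convention; the article mentions grading only for the calf test.

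**Step 2. Lumbar range of motion.** With no pre-intervention value there is no pre-to-post change. In a complete-case joint model that included the first visit, every participant would lack this value. A model restricted to the two later visits can be run, but its group-by-time interaction then asks whether the arm difference changes between those visits, not whether the intervention produced an immediate change.

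**Step 3. Can the effect of a shared model on power be stated?** The article does not describe a shared model. Suppose there were one. Assumptions: 50 × (1 − 0.30) = 35 evaluable per arm; nine primary variables (the SF-36 counted once, two pain scales); eight added secondaries; a two-group Hotelling test on one response per variable, with p and 70 − p − 1 degrees of freedom and noncentrality (35/2) × D², where D² is the squared Mahalanobis distance between arms.

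- *Secondaries add no separation.* D² = 1.02 gives 80% power at p = 9. The same D² at p = 17 gives 61%.
- *Other patterns.* Take a standardised effect of 0.67 on every primary and a common correlation of 0.3. Then D² = 9 × 0.67² / (1 + 8 × 0.3) = 4.04 / 3.4 = 1.19, and power with the primaries alone is 0.87. Adding eight secondaries:

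| Effect on each secondary | D² | Power, p = 17 |
|---|---|---|
| 0.67 | 1.32 | 0.76 |
| 0.35 | 1.41 | 0.79 |
| 0.20 | 1.93 | 0.92 |
| 0 | 3.08 | above 0.99 |

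Power falls in some rows and rises in others, because correlated variables with little effect act like covariates. The article gives no correlations or secondary effect sizes, so the sign of the change is unknown. These figures show only that indeterminacy. They are not properties of the trial.

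**Step 4. Can a false-positive rate be stated?** Eight independent, ungrouped tests at 0.05 would give 1 − 0.95⁸ = 0.34. The plan does not describe that procedure: follow-on ANOVAs depend on a significant multivariate interaction, and the number of models is not given. The figure does not transfer.

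**The case against.** **The roles do not strictly exclude testing.** A reader might infer that the article bars any test on a secondary measure. It does not: it never says that the primaries alone assess the intervention, nominal tests can serve hypothesis-building, and flexibility is given an explicit effect-assessing purpose. This stands. The sections are in tension rather than flat contradiction, and what is missing is any sign in the analysis rule that the secondary tests are exploratory.

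**No joint model is stated.** A reader might infer that primaries and secondaries enter a single MANOVA and that power drops from 80% to about 61%. The text names one method for both tiers but refers to its multivariate tests in the plural, and the differing visit schedules make one model for everything implausible. This stands too. The power loss depends on an assumed pattern, and Step 3 shows that the opposite can occur.

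**The false-positive figure.** A reader might infer a chance of about one in three of a spurious secondary finding. That ignores the interaction test that must be significant first, so it is not claimed.

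**Detail for the full plan.** Grouping outcomes into models is commonly left to a full protocol or SAP, and its absence here is not the complaint. The complaint is about what the article does state: one method for all outcomes, including some that it cannot handle.

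**Only some measures are affected.** The straight-leg raise also yields an angle and a pain score, and four other measures raise no problem of form. That limits the misfit; it does not remove it.

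**Conclusion.** The point holds in a limited form. The Data analysis section prescribes the same repeated-measures MANOVA at 0.05, with the same follow-on tests, for both tiers. That sits badly with the descriptive role given to the secondaries, and the method is wrong for all or part of four of the eight: the neurological screen, the yes/no straight-leg-raise signs, the instability test and lumbar range of motion.

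If the tiers shared a model, secondary measures could mask an effect on the primaries or produce a significant result themselves. The document fixes neither the model nor the correlations and effects needed to say which, so no numerical consequence is asserted. The sample size is not affected by this point. The assumptions behind the verdict are that reflexes and muscle tests are recorded as ordered grades, and that the rule is meant to cover every secondary measure, as its wording says.

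**What to change.** Amend the Data analysis section in one or two sentences to say that:

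- secondary measures are kept out of any MANOVA used to judge the intervention on the primary outcomes;
- all secondary analyses, including flexibility, are labelled exploratory and reported as between-arm differences with 95% confidence intervals;
- yes/no findings (instability, crossed straight-leg raise, positive straight-leg raise) are analysed as proportions, for example with a risk difference, and reflexes and muscle grades as ordered categories;
- lumbar range of motion is compared between arms only at the post-intervention and one-year visits.

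Flexibility keeps its stated purpose, with its result reported as exploratory. No new data, visits or participants are needed. The small cost is that a significant secondary result can no longer be presented as confirmatory evidence of effect.

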#### Secondary outcome measures

The Fear Avoidance Belief Questionnaire (FABQ) is a secondary "participation" outcome measure in our study. It focuses specifically on a subject's belief about how physical activity and work affects low back pain [46]. Fritz et al [47] determined that screening for fear-avoidance beliefs may be useful for identifying subjects at risk of prolonged disability and work absence.

Secondary "activity" outcome measures include the 24-hour Physical Activity Scale (PAS) and the 5-minute walk test. The PAS is a survey that requires the subjects to estimate the amount of time spent at different types and levels of physical activity during a typical day [48]. Its purpose is to monitor the level of activity in the subjects enrolled in the study, both as an outcome measure as well as an activity-monitoring strategy for all subjects. The 5-minute walk test will measure how far each subject can walk in a 5-minute period. The speed is self-selected by the subject. Excellent test-retest reliability (ICC = 0.99) has been established for this measure [42].

Secondary "physical" outcome measures include the following tests: lower quarter neurological screen, straight leg raising (SLR), lower quarter flexibility, lumbar spine range of motion, and lumbar spine instability. The purpose of the lower quarter neurological screen is to assess sensation, strength, and deep tendon reflexes (DTRs) before and after the intervention. The screen was derived from several different sources. The sensory testing points were derived and modified from the American Spinal Injury Association (ASIA) screen [49,50]. Sensation to pin prick (sharp/dull discrimination), light touch, and vibration (using a 256-Hz tuning fork) will be assessed. The muscles chosen for manual muscle testing were also derived from the ASIA screen. The muscle testing procedure was derived from Kendall et al [50]. Gastrocnemius/Soleus (S1) manual muscle test grading was based on the work of Lunsford and Perry [51]. Patellar and Achilles DTRs were assessed.

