### Sample size

Power calculations were based on data from prior published studies [23,24,42,44,57]. These data indicated that the inter-subject variability with respect to impairments, activity, and participation, was moderate to high. Since the outcome measures assess the immediate and long-term effects of rehabilitation in addition to surgery, the calculations were made on the assumption that the changes due to exercise and education will be greater than those expected for education alone. A 50% difference between groups (education, and exercise plus education) is expected based on prior studies, and a 30% subject attrition rate is anticipated. The possible attrition rate is attributed to length of the rehabilitative program, elimination of symptoms, or increase of symptoms and need for a second surgery. All power calculations were based on an alpha level of 0.05 and power of 0.8. Therefore, accounting for attrition, each group would need approximately 50 subjects.

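### Binary and graded secondary signs are assigned to a mean-based repeated-measures MANOVA, which does not suit their scale and shows only new minus resolved findings

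*Protocol article*

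**What the plan says.** The Data analysis section of the protocol article gives one method for all outcomes: "The primary and secondary outcome measures will be assessed for immediate and long-term effects using two-factor multivariate analysis of variance (MANOVA), with repeated measures for" (the repeated factor is the visit). The follow-on steps also compare means. Main effects are reported when there is no interaction; otherwise, "If significant interactions are found, then one-way ANOVAs will be performed for each main effect", with post-hoc pairwise tests as needed. Categorical measures are not excepted.

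The Secondary outcome measures section lists a neurological screen, straight leg raising and lumbar instability among the secondary physical outcomes. Their scales are described as follows.

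- Sensation: "Sensation to pin prick (sharp/dull discrimination), light touch, and vibration (using a 256-Hz tuning fork) will be assessed". Pin-prick is a two-way discrimination. No scoring is given for light touch or vibration.
- Strength: muscle tests are graded ("Gastrocnemius/Soleus (S1) manual muscle test grading was based on" a published method).
- Reflexes: assessed, with no scale stated.
- Crossed straight-leg raise: a sign that is noted.
- Passive straight-leg raise: an angle and a pain VAS, plus a definition of a positive test.
- Prone instability: if symptoms resolve fully when the legs are lifted, "it will be considered a positive test for instability of that segment".

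The aim of the screen is a before-and-after comparison: "The purpose of the lower quarter neurological screen is to assess sensation, strength, and deep tendon reflexes (DTRs) before and after the intervention". The Outcome measures section schedules all outcome tests before the intervention, after it and one year after surgery, and describes secondary outcomes as descriptive and hypothesis-building.

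**The concern.** There are two separate problems.

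The first is scale. MANOVA works with means and a covariance matrix of roughly normal responses. A sign that is present or absent, or a short grade on which many participants may sit at the normal end, does not meet that description. Where a sign is rare, the variance may be close to zero. This mismatch follows from the stated method and the stated measures; no event rate has to be assumed.

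The second is the question being answered. For a 0/1 sign, mean change is the number of new signs minus the number of resolved signs, divided by the number assessed. Participants enter with radicular pain and nerve-root tension signs, so some recovery is plausible. The Sample size section also foresees that some may get worse. When gains and losses occur together, the planned test sees only the balance. A real between-arm difference in new deficits could then appear as no group-by-time interaction.

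**Working it through.** **Inputs.** About 50 per group and 30% attrition (Sample size section) give 50 × (1 − 0.30) = 35 evaluable per arm. The figure of 50 cannot be reproduced uniquely, because no standard deviation, endpoint or sidedness is given. It is reached if, for example, the SD is 0.74 of the reference mean with a two-sided test: 2 × (1.96 + 0.84)² × (0.74/0.50)² ≈ 34.4, so 35, and 35/0.7 = 50. The point here does not depend on it. The documents give no frequencies for the signs, so **all counts below are assumptions**.

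**Method.** Take one sign at two visits and score each person's change as +1 (new), −1 (resolved) or 0. The group-by-time test is then a two-sample t-test on change:

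- mean change = (new − resolved)/n
- s² = [(new + resolved) − (new − resolved)²/n]/(n − 1)
- t = difference in means / √[(s²₁ + s²₂)/n], with 68 degrees of freedom

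The plan has three visits and several outcomes in one model. This is the simplest case of it.

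**Recoveries differ between arms** (n = 35 per arm, exercise against education):

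- 8 new/10 resolved against 1/3. Mean change is −2/35 in both arms, so t = 0 and p = 1.00. New signs are 8/35 (23%) against 1/35 (3%), Fisher p = 0.028.
- 7/7 against 1/1. Mean change is 0 in both arms and p = 1.00. New signs are 20% against 3%, a difference of 17 points (Newcombe 95% CI about 2 to 33). Fisher p = 0.055, so this case is borderline even when counted directly.

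**Recoveries equal between arms:**

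- 8/3 against 1/3. Means are 5/35 and −2/35, a difference of 0.200. The variances are 0.303 and 0.114, so t = 0.200/√(0.417/35) = 1.83 and p = 0.07.
- 8/2 against 1/2. Means are 6/35 and −1/35, a difference of 0.200. The variances are 0.264 and 0.087, so t = 0.200/√(0.351/35) = 2.00 and p = 0.05.

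Fisher's test on new signs gives 0.028 in both of these cases, so the loss is modest.

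**Does a different test cure it?** Suppose 10 of 35 are positive before the intervention in each arm, with 6 new and 6 resolved in the exercise arm and none in the education arm. Mean change is 0 in both arms (p = 1.00). Prevalence afterwards is 10/35 in both arms, so a categorical test of prevalence also gives p = 1.00. New signs among those negative at the start are 6/25 against 0/25, Fisher p = 0.022. Only a tabulation of change from each person's own starting finding shows the difference.

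**The case against.** **The cancellation is a special case.** It is exact only if exercise raises new deficits and recoveries by the same number. The first illustration also needs at least 10/35 (29%) of the arm to have the sign beforehand, which sits badly with signs that are mostly normal. This stands. The illustrations show what can happen, not what is likely, and the scale mismatch is the firmer half of the point.

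**The cancellation is not peculiar to MANOVA.** Any net or prevalence comparison shares it. This also stands, and it is why replacing one test with another would not be enough.

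**A reader might infer that new deficits would go unreported.** The documents do not support that. The Data analysis section names an inferential method and does not exclude counts or tables. The Methods/design section names a data monitoring and safety board. Detailed safety reporting is something an article commonly leaves to the full protocol.

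**A reader might also infer that these signs are the only objective, blinded record of deterioration.** They are not. Blinded evaluators administer all face-to-face measures, and the timed walk, sit-to-stand, modified Sorensen test and straight-leg-raise angle can all show worsening. The instability and crossed straight-leg-raise findings depend partly on what the participant reports.

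**The Sample size wording concerns dropout.** The phrase "elimination of symptoms, or increase of symptoms and need for a second surgery" is given there as a reason for attrition. Participants who leave for that reason would be absent from any table of those assessed. That stands, and the fix has to allow for it.

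**Conclusion.** The point holds as a mismatch between stated method and measurement scale, at low severity. The article sends every secondary outcome to a mean-based MANOVA, although pin-prick discrimination, muscle grades, the two straight-leg-raise signs and the instability test are binary or graded. Whether reflexes, light touch and vibration belong with them cannot be settled, because their scales are not given.

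The size depends on counts that the documents do not supply. In the assumed cases, a 23% against 3% difference in new signs ranges from invisible (p = 1.00, when recoveries differ to match) to slightly weakened (p = 0.05 to 0.07 against 0.028, when recoveries are equal). The trial's main conclusions do not rest on these outcomes, which are hypothesis-building. The supportable claim is that the planned analysis would not by itself show a difference in new deficits. Whether such deficits would be reported elsewhere is not something the article settles.

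**What to change.** In the Data analysis section, restrict MANOVA and ANOVA to the continuous measures, including the straight-leg-raise angle and its pain VAS. For the binary and graded signs:

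- State how each item is scored, including reflexes, light touch and vibration, and what counts as worse for each.
- Tabulate by arm, at post-intervention and at one year, the number and percentage worsened, improved and unchanged from the participant's own pre-intervention finding.
- Give the between-arm difference in proportion worsened with a 95% confidence interval by an exact or score-based method.
- State for each arm and visit how many participants were not assessed and why, for example after a second surgery.

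The cost is a few sentences and one table from data already collected at three visits, with no new tests or participants. The drawback is wide intervals for rare signs, which is an honest reflection of about 35 evaluable participants per arm.

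### Repeated-measures MANOVA discards participants with any missing value, although 30% attrition is anticipated for partly outcome-related reasons, and it does not fit the data collected after year 1

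*Protocol article*

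**What the plan says.** The Data analysis section of the protocol article names one method for everything: the primary and secondary outcomes will be "assessed for immediate and long-term effects using two-factor multivariate analysis of variance (MANOVA), with repeated measures for time". The abstract repeats this. The work is to be "performed using the SAS system, version 8.2", with no procedure named.

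The visit schedule is spread over several sections:

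- **Outcome measures:** "Testing of all outcome measures will be administered at the post-surgical/pre-intervention assessment, post-intervention assessment, and 1-year post-surgical assessment". After that, questionnaires and pain scales only, every six months. Partly completed questionnaires are not entered.
- **Secondary outcome measures:** because of post-surgical restrictions, "lumbar ROM will only be measured immediately following the intervention and one year after surgery".
- **Follow-up period:** each mailing follows a telephone call. Participants who report symptoms are sent the Oswestry, Roland-Morris, SF-36, SQOL, FABQ, PAS and pain scales. Those who report none are sent the PAS alone.
- **Sample size:** 30% attrition is anticipated, "attributed to length of the rehabilitative program, elimination of symptoms, or increase of symptoms and need for a second surgery", and the figure of about 50 per group is said to account for it.

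**The concern.** Classical repeated-measures MANOVA needs a full response vector from each participant. Someone who lacks one included value at one included visit drops out of the test, and the values already collected from that person are lost with them.

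The protocol's own reasons for attrition make this loss informative. Symptom resolution, symptom increase and second surgery are all related to outcome. Programme length bears on the exercise arm, since the control arm has a single education session. The participants left in the analysis need not represent the groups as randomised.

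The schedule adds a second difficulty. Some outcomes have no planned value at some visits, and after year 1 most primary outcomes are collected only from people with symptoms, a state the treatment is meant to change. Effects up to five years are a stated purpose of the trial, so this affects a main question.

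**Working it through.** **1. The plan's own figure.** The inputs are "All power calculations were based on an alpha level of 0.05 and power of 0.8", a 50% difference ("A 50% difference between groups (education, and exercise plus education) is expected based on prior studies") and variability described only as "inter-subject variability with respect to impairments, activity, and participation, was moderate to high". With no mean or SD, 50 per group cannot be derived directly. Working back, 50 × 0.7 = 35 evaluable per arm. The standardised difference detectable with 80% power, two-sided (sidedness is assumed), is (1.960 + 0.842) × √(2/35) = 0.67. Forwards, 2 × (2.802/0.67)² ≈ 35, and 35/0.7 = 50. The figure is attainable and already carries the 30%. The t-based equivalent is 0.68 SD. Both effect sizes are back-solved assumptions, not figures from the article.

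**2. Assessments.** Pre-intervention, post-intervention and 12 months, then 18 to 60 months every six months (8 mailed rounds), make 11. Each outcome followed throughout has 10 time contrasts.

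**3. Through year 1.** There are nine primary scores if the SF-36 counts as one (Oswestry, Roland-Morris, SF-36, SQOL, walk, sit-to-stand, Sorensen, two pain scales). Over three visits that is 9 × 2 = 18 contrasts. With eight SF-36 scores it is 16 × 2 = 32. Seventy completers give 70 − 2 = 68 error df, so even a joint test is computable.

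Missed visits beyond the 30% would reduce the 70. At an assumed 95% completeness per visit, 70 × 0.95³ = 60 remain over three visits and 70 × 0.95¹¹ = 40 over eleven.

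**4. After year 1, by design.**

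- *All primary outcomes, 11 assessments:* the walk, sit-to-stand and Sorensen tests are not scheduled after year 1, so there are 0 complete cases.
- *Questionnaires and pain scales only, 11 assessments:* a complete case must be symptomatic at all eight calls. Assume 30–40% of 70 are symptomatic at each call, taken from the 60–70% long-term success rate in the Background. If they are always the same people, 70 × 0.3 = 21 to 70 × 0.4 = 28 remain. With latent correlation 0.5–0.9 between calls, about 2–16 remain. If calls are independent, 70 × 0.4⁸ = 0.05, so fewer than one.
- *Secondary outcomes including baseline and lumbar range of motion:* 0 complete cases, because range of motion has no baseline.

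**5. Power over 11 assessments if all 70 were complete** (that is, if the questionnaires did go to everyone). Noncentrality is (35 × 35/70) × D² = 17.5 × D². With D = 0.68 in one contrast it is about 8.1.

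| Reading | Contrasts | Test | Power | Power at 5 × D² (arbitrary) |
|---|---|---|---|---|
| Six mailed primary measures jointly | 6 × 10 = 60 | F(60, 68 − 60 + 1 = 9) | 7% | 21% |
| One outcome at a time | 10 | F(10, 68 − 10 + 1 = 59) | 38% | 99% |

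A seventh score in the joint model gives 70 contrasts against 68 error df, and the test cannot be computed.

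**6. Effect of symptom-dependent mailing.** As an illustration, take a normal outcome at one late visit, a true difference of −0.67 SD, and 30–40% of controls symptomatic. Among those mailed, the difference shrinks to about −0.15 to −0.17 SD, from about 11–14 control and 4–6 exercise participants out of 35 per arm.

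**7. What a per-outcome mixed model retains.** At 0.67 SD, simple two-sample power is 80% with 35 per arm, 85% with 40, 89% with 45 and 92% with 50. The last is an upper bound, because a participant with no value after baseline adds little or nothing.

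**The case against.** The strongest reply is that the article nowhere says all outcomes enter one model. It refers to its multivariate tests in the plural, and a separate group-by-time test per outcome, domain or period also fits its wording. That stands. The 7% figure belongs to one reading only, and 38% is the counterpart for single outcomes. Separate models remove the dimension problem. They do not remove deletion of incomplete cases, the questionnaires withheld from asymptomatic participants, or the missing range-of-motion baseline.

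A reader might infer that the plan loses at least 30% of patients for outcome-related reasons. The article does not support that. The 30% is an anticipated figure tied to no visit, the pre-post comparison may lose less, and programme length is arm-related rather than outcome-related. The sample size already allows for the loss. No method has values from people after they leave; MANOVA's additional cost is the values they gave before leaving.

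A reader might also infer that nothing is left for any long-term test. Long-term assessment starts at one year, when all outcomes are scheduled, and the analysis to that point is feasible.

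The secondary outcomes are described as hypothesis-building and the range-of-motion exception is explained, so those points carry less weight. Missing-data handling and outcome grouping may also sit in a fuller plan. That is fair as to omissions, but the method criticised here is the one the article states.

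**Conclusion.** The concern holds in a limited form. The named method by default deletes anyone with an incomplete record, while the protocol anticipates 30% attrition for reasons partly linked to outcome and partly to arm. The consequence through year 1 is possible selection bias and discarded data, not a failure of planned power.

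After year 1 the method does not fit the data. There is no complete case for all primary outcomes over 11 assessments. For the questionnaires alone there are between fewer than one and 28, depending on how persistent symptoms are, if 30–40% are symptomatic at each call. The main cause at that stage is the mailing rule, which conflicts with the Outcome measures section.

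These conclusions rest on default complete-case behaviour, since no SAS procedure is named. The power figures rest on the assumed 0.68 SD and on 70 complete participants.

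**What to change.** - Replace the MANOVA with one likelihood-based linear mixed model per outcome (PROC MIXED, in the SAS version already named). Include all randomised participants as allocated and every available value at that outcome's own visits, with terms for arm, visit, arm-by-visit and baseline.
- Use an unstructured covariance, with a prespecified simpler structure if it does not converge. Over 11 visits the unstructured form has 11 × 12/2 = 66 parameters for about 100 participants, so the fallback matters.
- Compare lumbar range of motion between arms at its two measured visits, and state it as an exception to the sentence that all outcomes are tested at baseline. Use logistic models for positive/negative signs.
- Reconcile the Follow-up period section with the Outcome measures section so that the questionnaires and pain scales go to all participants at every mailed round. The model change alone cannot recover values withheld by design.

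The mixed model still assumes that missingness is explained by the observed data, so continued collection from participants whose symptoms resolve or worsen is part of the remedy. The cost is slightly more analysis work and some additional mailed questionnaires. No new software is needed.
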